### Data confidentiality

During field investigations, a file with a name and address and corresponding barcode assigned to the subject identity will be used. This file will only be accessible to the field investigations team members who have direct contact with the participants. To ensure confidentiality, the file will be kept in an access-limited and secured (locked) cabinet. Upon completion of the field work, the address of the individual will be removed from the database, with irreversible anonymisation. Fieldwork will involve initial paper files that will then be input into an electronic file which will be accessible only to the field investigation team.

Study compliance will strictly adhere to the Republic Act No. 10173 (Philippines Data Privacy Act) stipulating full protection of an individual’s personal information by coding and secure data storage, with no dissemination of this information outside the study context. Participants can request their personal information to be removed and destroyed at any time during the study, which will also result in the withdrawal of the participant from the study.

### Intervention (Fig. 3)

Throughout the study period, local health authorities will continue with their routine government approved dengue control strategies. Our intervention study will in no way replace the current mosquito control methods in use.

**Fig. 3 Fig3:**
[figure not shown]
Time schedule of enrolment, interventions, and post-allocation data collections (based on SPIRIT 2013 figure [37]). HH Household

For the intervention study, 46 clusters will be selected each covering an area with at least 100 children. Mean child (age 6–16 years) densities in urban sites are 18/ha (/0.01 km^2^). Thus, an average sampling radius of 140 m (6.15 ha) would generate 100 children (excluding 10% outright refusal) to be recruited with an additional 50 m radius buffer zone for treatment but without saliva sampling. The area to be treated would thus be 113,000 m^2^ per cluster and would require 113 AD devices at a density of 1 trap/1000 m^2^ per treated cluster (23 study clusters to be treated). Before geolocalisation of historical dengue cases, however, we cannot predict which sites will be selected, nor their actual human densities, and thus the initial calculations are based on mean densities.

Treatment of areas with In2Care® devices will be carried out for 4 months each year and the active ingredient sachet (combination PPF + fungus) replaced every 6 weeks. Each In2Care® trap will be assembled (Additional file 2) and filled with 3.5–4.5 l of clean tap water. One pesticide-treated netting removed from the active ingredient sachet will then be placed on the floater and the remaining contents of the sachet tipped into the water. Each (10 × 18 cm) sealed aluminium refill sachet contains: 0.5 g In2Mix (containing 10% *Beauveria bassiana* strain GHA (Chemical Abstracts Service (CAS) No. 63428–82-0), 74.03% pyriproxyfen (CAS No. 95737–68-1), 0.97% pyriproxyfen impurity, and 15% insert silicon dioxide); one 5 × 49 cm gauze strip; and two yeast food supplement tablets of common brewer’s yeast (*Saccharomyces cerevisiae*). The tablets are added to the trap tap water to emit organic odours attractive for egg-laying mosquitoes.

In2Care® traps will be placed in open areas outside of the house. GATs will be placed inside and outside houses at designated locations. GATs will be assembled as per the manufacturer’s instructions and filled with water to which a handful of dry grass/hay will be added. A sticky strip is placed inside the GAT and used to capture entering mosquitoes (Additional file 3). The general state of the traps (In2Care® and GATs) will be assessed during the weekly GAT counts and water replenished where necessary. Likewise, the dried grass and water in the GATs will be replaced during the weekly survey. After 6 weeks, the netting, active ingredient, and yeast tablets from the sachet of the In2Care® mosquito trap will be replaced with a new sachet and new water. At the end of the 4-month treatment period, all mosquito traps will be removed, properly cleaned, and stored until the following year.

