### Study type

The study is a parallel, two-armed cluster randomised trial (PCRT) evaluating the efficacy of the In2Care® mosquito trap for reducing incidence of dengue infection over a 2-year period using 4 consecutive months of treatment each year.

Previous studies have estimated that, to account for the unpredictable spatio-temporal heterogeneity in dengue transmission, PCRTs are the most effective study design and that a larger number of clusters with fewer children per cluster provide the optimal strategy—in effect, a bet-hedging approach for a statistically sufficient coverage of an area [31]. In order to attempt to control for the spatial heterogeneity in dengue occurrence, 46 areas (hereafter referred to as “clusters”), each of approximately 200 m in radius, will be pre-selected. Twenty-three clusters will be assigned to the treatment arm with In2Care® traps and 23 to the control arm without traps. Cluster sites assigned to treatment versus control arms will be matched according to retrospective incidence of reported dengue clinical cases over the previous 5 years and human population density (See Stratification scheme below). Because of ‘edge effects’, where individuals near the periphery of the treatment area will be potentially subject to contact with mosquitoes coming from neighbouring non-treated areas, we will implement the “fried egg” design [32] whereby we will assess sero-conversion only in children resident at least 50 m from the treatment zone edge. Thus, whilst we will implement In2Care® traps throughout a 200 m radius circle, we will only consider sero-conversion in children within a 150 m radius (Fig. 1). One hundred schoolchildren (between 6 and 16 years of age) will be recruited for repeated sero-conversion observation within the inner circle of each of the 46 clusters (See Sample size calculations below). As the population density in clusters will vary, it is possible that there will not be sufficient children within a prescribed area. In this case, we will increase the circle radius to reach the required sample number.

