### Recruitment

In each *barangay* pre-selected to participate in the study, Research Institute for Tropical Medicine (RITM) team members will hold general information meetings on the project with the population in the presence of the community (*barangay*) health workers (BHWs) and local public health officials. Because the volunteers to be recruited are of school age, additional information meetings will be held in the local schools. Once clusters are identified and randomly assigned with appropriate stratification, the study team will perform household visits with the Lipa City public health staff and respective area BHWs. The visit will explain the study and study protocol in detail and request individual informed consent/assent for periodic saliva sampling and mosquito trap placement by each household head (In2Care® and/or GATs) in and around participant’s houses (See Ethics approval and consent to participate below).

Following signed consent, a short questionnaire pertaining to the participant will be completed and the individual assigned a unique identifier barcode. The questionnaire will be completed on paper including details on: name, address, age, sex, whether having received the Dengvaxia® vaccine (and if yes, how many injections) or not, and the attending school and year (grade). The individual’s barcode will be placed next to their name on the consent form and kept in a separate file. Subsequent samples will also be labelled with a unique barcode and linked back to the individual’s barcode in the questionnaire.

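### The floor of 100 children per cluster leaves no room for the plan's own 10% refusal, and the circle-enlargement rule is not confined to the time before allocation

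*Protocol article*

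**What the plan says.** Four places in the protocol article bear on how many children a cluster must hold and how its boundary is drawn.

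- **Target.** Under Study type, one hundred schoolchildren "will be recruited for repeated sero-conversion observation within the inner circle of each of the 46 clusters". The same section describes a 200 m treated circle and a 150 m sampled circle, and admits only children living at least 50 m inside the treated edge.
- **Floor.** Under Intervention, "46 clusters will be selected each covering an area with at least 100 children".
- **Sizing.** The same Intervention paragraph then gives a density: "Mean child (age 6–16 years) densities in urban sites are 18/ha". From this it derives that "an average sampling radius of 140 m (6.15 ha) would generate 100 children (excluding 10% outright refusal) to be recruited". Outside that circle it places a 50 m ring that receives traps but is not sampled. It gives a treated area of 113,000 m² and 113 devices per cluster, and calls these initial calculations at mean density.
- **Shortfall.** Study type notes that density varies and a given area may hold too few children, then adds: "In this case, we will increase the circle radius to reach the required sample number".

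The order of events is in Recruitment: "Once clusters are identified and randomly assigned with appropriate stratification, the study team will perform household visits". Consent is sought at those visits.

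**The concern.** The floor and the target are the same number, 100, although the plan expects one family in ten to refuse. A cluster admitted at the floor will fall short of its target, and the stated remedy for a shortfall is a larger circle.

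That remedy is loosely fixed in two ways. First, it runs until the required sample number is reached. That number is a count of recruits, and recruits are counted at visits made after the arms are assigned. Control clusters get no In2Care traps, so families and field staff will know the arm, and the request put to households (saliva sampling and trap placement) need not be the same in both arms. If uptake then decides how far a cluster extends, the set of eligible children depends on the allocation, which is a known route to recruitment bias in cluster trials.

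Second, Study type describes two circles, but the rule enlarges only one, unnamed. If the sampled circle grew inside a fixed trap zone, some treated children would live closer to untreated ground than the plan allows, and the measured trap effect would be diluted.

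**Working it through.** **Inputs (protocol article).** Density 18 children/ha, sampling radius 140 m (6.15 ha), refusal 10%, buffer 50 m and 1 device per 1000 m² (Intervention); inner radius 150 m and outer radius 200 m (Study type); incidence 3%, 50% reduction, 2054 per arm and 250 dropouts per arm (Sample size calculations).

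**1. The plan's own figures reproduce.**
- Recruits = density × area × (1 − refusal) = 18 × 6.15 × 0.90 = 99.6, against 100 stated. Residents = 18 × 6.15 = 110.7.
- Treated area = π × 190² = 113,411 m², or 113 devices, as stated.

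**2. The floor.**
- Recruits at the floor: 100 × 0.90 = 90, which is 10 short.
- Residents needed: 100 / 0.90 = 111.1, so 112 (expected yield 112 × 0.90 = 100.8).
- Clusters with 100 to about 111 residents pass the floor but fall short of 100 in expectation.

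**3. Radius that would restore 100 recruits in a cluster at the floor.** At constant density within the cluster, area must grow by 1/0.90, so new radius = old radius / √0.90.
- From 140 m: 147.6 m. Buffer if the outer circle stays at 190 m: 42.4 m.
- From 150 m: 158.1 m. Buffer if the outer circle stays at 200 m: 41.9 m.
- A 140 m circle enlarged inside a 200 m zone would still have 52.4 m, so the result depends on which pair of radii applies.
- If the outer circle moves as well, the buffer stays at 50 m. At the stated trap density, devices become π × 197.6² / 1000 ≈ 123 (from 113) or π × 208.1² / 1000 ≈ 136 (from 126).

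**4. Bound on the loss if there is no enlargement.** With p = (0.03 + 0.015)/2 = 0.0225, the plan's formula solved for power gives Z(1−β) = √[n × 0.015² / (2 × 0.0225 × 0.9775)] − 1.96.
- 100 per cluster: 23 × 100 − 250 = 2050 retained per arm, Z = 1.28, power about 90%.
- Every cluster exactly at the floor: 23 × 90 − 250 = 1820 per arm, Z = 1.09, power about 86%.

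This is a worst case, and like the plan's formula it ignores clustering.

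**5. Timing, from the text.** Study type gives density as the reason for enlargement and reaching the sample number as its end point. Density can be known when clusters are chosen; the number recruited cannot. Recruitment puts consent after assignment. No sentence says that enlargement ends at allocation.

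**The case against.** The best defence is that the plan does allow for refusal. Its average circle is sized net of refusal, and the floor could be read as 100 recruitable children, which the following sentences convert into an area. Enlargement is tied to density, clusters are described as pre-selected, and the radii are called initial, so adjusting circles at selection, before allocation, fits every passage. The 50 m rule is explicit, and Intervention adds the buffer to whatever the sampling radius is. A condensed article may also leave boundary drawing to the full protocol.

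Much of this stands, and it rules out several stronger readings that a reader might infer:

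- *That the plan overlooks refusal.* It does not; the arithmetic for the average cluster is right.
- *That circles will be enlarged during enrolment.* The documents do not say so. They leave it open.
- *That the plan gives up its buffer.* No passage lets it shrink. It would do so only if the inner circle alone grew, against the stated rule.
- *That only about half of the 100 children live in the sampled circle.* Study type places the 100 recruits in the inner circle, and Intervention ties them to the sampling radius.
- *That enlarged clusters leave a 300 m zone on which risk was classified.* In Statistical analyses, 300 m is the minimum scan diameter, and risk is assigned by purok.
- *That uptake far below 90% would cause large boundary shifts.* The only refusal figure given is 10%; anything lower is an assumption.

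The defence does not answer the text as written. The floor carries no refusal margin, and the remedy is governed by a recruit count that becomes known only after assignment. This is a stated rule fixed loosely, not detail left to another document.

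**Conclusion.** The point holds in a limited form. Read as resident children, the floor is inconsistent with the plan's 10% refusal: about 90 recruits at the floor, with 112 residents needed for 100. The defect touches only clusters holding 100 to about 111 children; how many of the 46 these are cannot be known from the article. The enlargement rule, followed literally, permits a consent-driven boundary change after the arm is known, and does not say that the trap zone follows the inner circle. For a cluster at the floor with only the inner circle enlarged, the buffer would be about 42 m instead of 50 m.

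These figures assume 10% refusal, uniform density within the cluster, and an outer circle held at the matching 190 m or 200 m. The result is a risk of bias that the wording allows, not a bias that the plan prescribes. It should be corrected because the trial is open at household level and the correction is nearly free.

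**What to change.** 1. State the floor as at least 112 resident children aged 6–16 inside the inner circle, that is, 100 net of 10% refusal.
2. Set each cluster's inner radius from the resident child count before randomisation.
3. State that the outer circle moves with the inner one, so that the 50 m buffer is kept in every treated cluster.
4. State that no circle is enlarged after allocation; a cluster that enrols fewer than 100 keeps its boundary.
5. Reconcile the inner radius of 150 m in Study type with the 140 m in Intervention, and the matching outer radii of 200 m and 190 m.

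**Cost.** A few sentences of protocol wording, and a child count, already needed to apply any floor, completed before allocation. Treated clusters enlarged at selection need about 10 more devices each in the example above. Some clusters may end slightly below 100: with independent consent at 90% (an assumption), a cluster with exactly 112 residents reaches 100 with probability about 0.67, and one with 118 with probability about 0.97. A somewhat higher floor would therefore buy more certainty, if enough sites can meet it.

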### Saliva sampling and biological analyses

A saliva sample will be taken by spitting into a sterile urine collection container, kept on ice, and transported to RITM for further processing. A 1-mL aliquot will be placed in a labelled Eppendorf® tube for storage at −20 °C. Sampling will occur just prior to, during (after 2 months of trap deployment), and at the end of the 4-month intervention period for 2 successive years. Sero-conversion testing will be performed using an in-house ELISA developed by Institut Pasteur [38] in duplicate on “paired” pre-/concurrent/post-samples from the same individual for each season. Although IgM titres will rise during a secondary DENV infection, a significant increase in IgM titres only systematically occurs in primary dengue infections and is relatively short lived; therefore, changes in IgG titres will be measured [38]. Exposure to dengue virus will produce an increase in IgG titre compared with the baseline titre in an individual, irrespective of whether they have been vaccinated or not or having been previously exposed to any DENV serotype (See Statistical analyses below). The technicians performing the ELISAs will have no prior knowledge whether the samples come from a treatment or control site. Upon study completion, analyses, and publication, all saliva samples will be destroyed and coding files erased.

### Specific data collection

For each participating child, information on their name, age, sex, address, *barangay*, cluster number, dengue vaccination status, school, class, and subsequent dengue ELISA titres will be recorded using a paper case report form that will be subsequently input into a study electronic database. Unique bar codes will be used as identifiers.

Data will be entered directly into DDMS (See Data management below) with 10% cross-checking.

Data will remain secured at the Entomology unit in RITM, Alabang, The Philippines. Statistical analysis will be performed in RITM.

After the final saliva sample has been taken and the data cross-checked for errors, the file linking the individual’s name and code will be destroyed.

### Benefits to the individual and the community

Study volunteers and their parents will be informed on their specific sero-conversion ELISA findings during an annual feedback meeting. Whilst not providing a definitive diagnostic for infection, at a minimum this will inform individuals whether they are sero-positive for dengue and whether they have had a primary or post-primary infection. Because there is an increased risk of severe disease in post-primary infections, this information could enable individuals to enhance their efforts for personal protection from mosquito bites. A major benefit of the study is directed to the entire community, and potentially the entire country and beyond, if there is evidence that the use of In2Care® mosquito traps can decrease the risk of dengue transmission.

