### Setting (Fig. 2)

Dengue is endemic throughout much of the Philippines, and between 2008 and 2012 the country’s Department of Health (DoH) reported an annual average of 117,065 diagnosed (symptomatic) dengue cases, although the number is likely to be far higher because of significant under-reporting [36]. Region IV-A (Calabarzon) has consistently had a high burden of dengue and was one of three regions where the dengue vaccine (Dengvaxia®, Sanofi Pasteur) was implemented. According to an official DoH report, in 2018 the Calabarzon region was the area most affected by dengue, accounting for 19% of all national cases, while also showing an increase in case load of 40% in comparison with the same time period the previous year. Lipa City is a large city in the Calabarzon region and is located approximately 78 km south of Manila at an altitude of 312 m, covering an area of 209.40 km^2^ with a population of 332,386 people in 2015. The city is subdivided into 72 *barangay*s of varying human density (at an average of ~ 1800/km^2^). The average annual temperature is 28 °C (82 °F) and the peak dengue transmission season typically occurs during increased rains from June to December.

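### The feedback to families promises primary/post-primary status, which IgG change alone does not supply for vaccinated children with baseline IgG or for seropositive children with no rise

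*Protocol article*

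**What the plan says.** *Benefits to the individual and the community* commits to individual feedback: "Study volunteers and their parents will be informed on their specific sero-conversion ELISA findings during an annual feedback meeting". The next sentence opens with a caveat, "Whilst not providing a definitive diagnostic for infection, at a minimum", and continues "this will inform individuals whether they are sero-positive for dengue and whether they have had a primary or post-primary infection". The section then gives the purpose: "Because there is an increased risk of severe disease in post-primary infections, this information could enable individuals to enhance their efforts for personal protection".

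*Saliva sampling and biological analyses* describes the assay. It notes that a significant IgM increase occurs systematically only in primary infection and that it "is relatively short lived; therefore, changes in IgG titres will be measured". Samples are paired within child and season. Exposure is said to raise IgG over the child's own baseline "irrespective of whether they have been vaccinated or not or having been previously exposed to any DENV serotype".

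*Sero-conversion*, under *Statistical analyses*, uses the result in two ways: a yes/no four-fold rise in IgG optical density, and the change in optical density itself. Vaccination status (0 to 3 inoculations) enters as an explanatory variable.

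On vaccination, *Setting (Fig. 2)* says that the study region "was one of three regions where the dengue vaccine" was implemented. *Study subject eligibility criteria* does not exclude vaccinated children. *Recruitment* records vaccination and number of injections per child, and *Specific data collection* puts vaccination status and ELISA titres on the same case report form.

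**The concern.** The feedback sentence offers more than the described measurement delivers. An IgG rise that occurs whatever the child's vaccination or infection history shows exposure; by itself it does not show whether the infection was the first. The baseline sample adds information on history, but only if baseline IgG can be read as past infection. In a population that includes vaccinated children, that reading is not always available.

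The article presents this as personal risk information about severe disease, so its accuracy matters to the families who receive it. A vaccinated child who has never been infected could be told that he or she is sero-positive for dengue. If that child were then infected for the first time, the infection could be reported as post-primary. Vaccination status is considered relevant enough to adjust for in the model, yet it has no stated role in the individual result.

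**Working it through.** The article gives no figure for this point, so the check sets the promised label against what paired IgG can show, group by group. IgG is taken to be dengue-specific, as the article takes it.

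| Child | Paired IgG pattern | What can be said | Label supported? |
|---|---|---|---|
| Unvaccinated | Negative at baseline, then rises | First infection | Yes, primary |
| Unvaccinated | Positive at baseline, then rises | Earlier infection plus a new one | Yes, post-primary |
| Unvaccinated | Positive at baseline, no rise | At least one past infection; one or several unknown | Undetermined |
| Vaccinated | Positive at baseline, with or without a rise | Source of baseline IgG unknown: vaccine, infection or both | Unreliable |

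In the last row the outcome depends on a history that the assay does not show. If the child had been infected before, sero-positive is correct, and post-primary is correct after a rise. If the baseline IgG is from vaccine alone, reading it as past infection is wrong, and calling a later first infection post-primary is wrong.

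**Can the number be derived?** It would need vaccine coverage *v* and the share ever naturally infected *s*. The article gives neither. The following is illustration only. It assumes that every vaccinated child is IgG positive and that vaccination is unrelated to past infection.

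- Vaccine-only IgG as a share of all children: *v* × (1 − *s*).
- As a share of IgG-positive children: *v*(1 − *s*) / [*s* + *v*(1 − *s*)].
- Low end, *v* = 10%, *s* = 90%: 0.10 × 0.10 = 1% of all children; 0.01 / 0.91 = 1.1% of IgG-positive children.
- Middle, *v* = 30%, *s* = 70%: 0.30 × 0.30 = 9%; 0.09 / 0.79 = 11.4%.
- High end, *v* = 50%, *s* = 50%: 0.50 × 0.50 = 25%; 0.25 / 0.75 = 33%.

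Applied to the planned 4,600 children, the extremes are 0.01 × 4,600 = 46 and 0.25 × 4,600 = 1,150. A 25-fold range resting on two assumed inputs is not an estimate. It shows only that the documents do not settle the size. Children whose first infection would be called post-primary are a subset of these, because they must also be infected during follow-up.

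**The case against.** The strongest reply has four parts.

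**The caveat.** The sentence begins by saying that the result is not a definitive diagnostic. That stands as a general warning about diagnosing infection. But the words that follow present sero-status and primary/post-primary status as the least that families will learn, and vaccine antibody is not mentioned.

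**Paired samples can separate primary from post-primary infection.** This stands for unvaccinated children with a rise. A reader might infer that the label will be wrong for every vaccinated or already seropositive child. The documents do not support that. A rise from a positive baseline in an unvaccinated child is correctly post-primary, a positive child with no rise is undetermined rather than mislabelled, and a vaccinated child with a true past infection is labelled correctly.

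**The full protocol or the cited in-house ELISA may contain a titre-based rule.** That cannot be excluded, and an article need not print result sheets. The point is narrower than missing detail: the article affirmatively promises a distinction that the method it describes does not make for some children.

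**The sections do not contradict each other.** This also stands. The IgM remark explains why IgG was chosen to detect exposure; it does not say that IgG pairs can never separate the two. The sections are mismatched in scope.

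A reader might also infer that misinformed families would relax their precautions. The text gives no support for this: it expects the information to lead families to enhance protection.

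**Conclusion.** The point holds in limited form. The feedback promise exceeds the described assay for two groups: vaccinated children with IgG at baseline, for whom the labels are unreliable (and wrong where the IgG is vaccine-only), and baseline-positive children with no rise, for whom primary/post-primary status is undetermined. For unvaccinated children with a rise, the promise is supportable.

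The number affected cannot be derived from the documents. It would be tempting to multiply 4,600 by an assumed coverage, for example 10% to 40%, giving 460 to 1,840. That would count every vaccinated child, including those correctly labelled, and would not measure mislabelling.

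Severity is low. The issue concerns what participants are told. The sample size and the efficacy analysis are unaffected. The conclusion assumes that no further classification rule exists in material not shown; if one does, the remedy is to state it and say how vaccination enters it.

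**What to change.** Reconcile *Benefits to the individual and the community* with *Saliva sampling and biological analyses* by limiting individual feedback to what paired IgG shows:

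- Report whether IgG was detected at baseline and whether it rose.
- Keep the primary or post-primary description for unvaccinated children with a rise, according to a negative or positive baseline.
- Make no primary/post-primary statement for vaccinated children with baseline IgG, or for baseline-positive children with no rise.
- Use the vaccination status already recorded to qualify results for vaccinated children, stating that the test as described does not separate vaccine antibody from past infection.

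This requires changes to the protocol text and the feedback material, with no new samples, tests or data items. The cost is less specific information for some families.
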